| Internal ref. no. (or short title) | PREVENT-PTSD                                                                                                                                                                                                                                                                                                                                                                                                                                    |                                                                                                                                                                                                              |
| Trial Design                       | Randomized controlled trial                                                                                                                                                                                                                                                                                                                                                                                                                     |                                                                                                                                                                                                              |
| Trial Participants                 | Students training to be paramedics at university in years 1, 2 or 3 of their university programme                                                                                                                                                                                                                                                                                                                                               |                                                                                                                                                                                                              |

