## BACKGROUND AND RATIONALE

Emergency workers carry a threefold increase, compared to the general population, in risk for major depression (MD) and posttraumatic stress disorder (PTSD), and an associated increased risk of poor physical health (1). To date, interventions aimed at reducing risk of ill mental health in this population have been unsuccessful. Randomized controlled trials (RCT) found that trauma risk management, a peer support system widely available to the police and ambulance services in England (2); critical incident stress debriefing widely used by UK fire-services (3), and the charity Mind's six-session group-based resilience intervention had no effect on resilience or rates of mental ill health (4) (Table 2). More effective preventative interventions for emergency workers are urgently needed.

Established interventions have likely been unsuccessful because they fail to target predictors of mental ill health and are offered to emergency workers after rather than before repeated exposure to the stresses linked to their work. Moreover, cognitive strategies that could help them cope with characteristic stressors are not included as part of the training. Our and others' research has demonstrated that exposure to trauma or stressful scenarios through imagery reduces anxiety for police officers (9) and other at risk populations (10). Development of more effective interventions requires identification of predictors of mental disorders and an understanding of how to modify them.

In a series of experimental and prospective studies, we identified two cognitive factors that are particularly powerful predictors of poor mental health in emergency workers: rumination (repetitive negative thinking) and resilience appraisals. Those who reported ruminative thoughts during critical incidents were more likely to experience poor levels of coping (5). Adaptive appraisals during analogue trauma lead to more successful attempts to regulate emotions and fewer PTSD symptoms (6). Our large-scale prospective study of newly recruited paramedics (1) investigated predictors of PTSD and depression derived from cognitive theories of PTSD and depression. Rumination at the start of paramedic training uniquely predicted PTSD; low resilience uniquely predicted an episode of major depression.

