#### 7.1.1 Inclusion Criteria

- Aged 18 and above.
- In years 1, 2 or 3 of student paramedic training.
- Access to internet.
- Willing to be randomly allocated.

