#### 8.4 Randomisation

Random allocation to the three trial conditions (iCT, Mind-Online, standard practice) will be at a 1:1:1 ratio, stratified by site and initial eligibility (above or below cut-off on PHQ-9 and PCL-5 at screening) by the Oxford Clinical Trials Research Unit (OCTRU).

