#### 8.5 Subsequent Assessments

Participants will complete assessments with an independent trained assessor who will be unaware of trial condition at baseline, 6, 52 and 104 weeks. They will also complete questionnaires on these occasions.

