## **STUDY METHODS**

### **Trial Design/framework**

#### **Interventions:**

The study is a single-blind (assessors blind) randomised controlled trial. There are three arms: iCT-R, Mind-Online, and Standard Practice. The newly developed intervention iCT-R aims to modify rumination and appraisals linked to low resilience and risk for PTSD and MDD with a six-session supported online intervention. A trained research assistant provides email feedback on students' responses and, through an automated SMS programme, sends regular reminders of key points of the intervention and notifications to practice the skills. The other intervention also contains six online modules and includes information and advice about stress, sleep problems, anger, depression, PTSD, and mindfulness. Participants will receive the same frequency, type and duration of online support as in iCT-R. The third

arm is Standard Practice. Participants have access to the usual support offered through their university, but they will not receive any online modules or online support.

Time points:

Data are collected pre-intervention, post-intervention, at 6-months follow-up, at 1-year follow-up and at 2-years follow-up.

More information on the intervention arms and measurement time points can be found in the published trial protocol ([name] et al., 2018).

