## **Analysis Methods**

Analyses of the primary trial objectives:

To analyse any differences between the intervention arms in terms of effectiveness with regards to rates of PTSD and MDD diagnoses (SCID-5) at 1-year follow-up (short-term primary outcome time point) and at 2-years follow-up (long-term primary outcome time point once completed), intervention condition and the interaction between intervention time and

intervention group on rates of PTSD and MDD diagnoses, logistic mixed effects models with PTSD and MDD diagnoses as outcomes (short-term outcome 1-year follow-up data, long-term outcome 2-years follow-up once completed) are specified and analysed.

To analyse any differences between the intervention arms in terms of effectiveness with regards to PTSD symptom severity (PCL-5) or MDD symptom severity (PHQ-9) at 1-year follow-up (short-term primary outcome time point) and at 2-years follow-up (long-term primary outcome time point once completed), intervention condition (categorical; iCT-R versus Mind-Online versus Standard practice; level 2) and the interaction between intervention time (categorical; post-intervention, 6-months follow-up; 1-year-follow-up, 2-year follow-up, once completed; level 1) and intervention group on PTSD or MDD symptom severity, linear mixed effects models with either PTSD or MDD symptom severity as outcomes are specified and analysed.

Both repeated assessments and intervention arm are specified as categorical variables for reasons of flexibility in the modelling approach. Repeated assessments/ time, intervention arm, both their interaction effects, and baseline scores and covariates are estimated as fixed effects and random effects are estimated for time (level 1) nested within the participants (level 2). An unstructured variance-covariance matrix is used to model the error correlation structure within the participants. Estimation method is Maximum Likelihood. Normality of the residuals for the outcomes is confirmed visually.

Randomisation has been done by stratification by site, gender, and baseline PTSD symptom severity and MDD symptom severity. Therefore, baseline PTSD symptom severity and MDD symptom severity and randomisation factors are added as covariates in these models. Site is added as random factor in those models. If non-significant, they will not be carried forward into further analyses.

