## Main trial analyses and Covid:

Descriptive statistics for the two outcome measures for the primary trial objectives (PTSD and MDD diagnoses and PTSD or MDD symptom severity) are reported for the whole sample and by intervention groups based on the Covid grouping variables for the short-term primary outcome time point at 1-year follow-up and the 2-year follow-up assessment point, once completed (means and standard deviations for continuous outcomes and absolute numbers and percentages for diagnoses).

In the case of any differences, additional analyses are carried out to explore whether there is any possible intervention heterogeneity depending on participants' Covid status on PTSD and MDD diagnoses or PTSD and MDD symptom severity at 1-year follow-up or at 2-year follow-up, once completed. In this case, linear and logistic mixed models are specified in the same way as proposed for the analyses of the primary trial objectives and participants' Covid status variables are entered as exogenous time-varying covariates. Two-way interaction terms between those covariates and intervention group as well as three-way interaction terms between Covid status, time, and intervention group are analysed. In the case of significant interaction terms, which could possibly indicate intervention heterogeneity, additional effect size measures are reported. Adjusted mean differences and Cohen's  $d$ 's with standard deviation at baseline in the denominator are reported in tables for continuous outcomes from results of linear mixed effects models and frequencies of diagnoses (absolute numbers and percentages) and absolute differences as well as odds ratios are reported for dichotomous outcomes.

In addition to Covid status depending on time points, the COVID questionnaire, scored as a continuous variable, which assesses the self-reported impact of COVID on a participant will be descriptively reported and analysed as a covariate in a similar way like the time-based covariates to determine whether or not it influences outcome. We will compare rates of PTSD and MDD for the sample who score positive on the item ('I am graduating

early as a result to support the NHS workforce') compared to participants who do not endorse this item.

Exploration of missing data patterns and possibly additional sensitivity analyses:

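### Year of training is left out of the primary and secondary models, and the Covid early-graduation comparison is confounded by career stage

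*Combined protocol and SAP*

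**What the plan says.** **Eligibility and follow-up.** Protocol 7.1.1 admits students "In years 1, 2 or 3 of student paramedic training". Protocol 8.5 applies one schedule to all of them: "Participants will complete assessments with an independent trained assessor who will be unaware of trial condition at baseline, 6, 52 and 104 weeks".

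**Stratification.** Protocol 8.4 stratifies by site and by screening status on the PHQ-9 and PCL-5. SAP 3.2 (Randomisation and Blinding) lists site, gender and the two symptom cut-offs. Neither lists year of training.

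**Models.** For the primary objectives, SAP 6.2 (Analysis Methods) states: "Therefore, baseline PTSD symptom severity and MDD symptom severity and randomisation factors are added as covariates in these models". Site enters as a random factor. The secondary models use the baseline value of the outcome, baseline PTSD and MDD severity and the randomisation factors. Year appears in neither set. The one pre-specified subgroup (SAP 6.5) is baseline symptom severity.

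**Rationale.** Both background sections suggest that earlier interventions failed in part because they "are offered to emergency workers after rather than before repeated exposure to the stresses linked to their work".

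**Covid analysis.** Under SAP 6.6, for a COVID questionnaire item on graduating early to support the NHS, the plan is: "We will compare rates of PTSD and MDD for the sample who score positive on the item". The comparison group is everyone who does not endorse it.

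**The concern.** Year of training is a baseline characteristic that every participant must have on record to be eligible. It plausibly relates to prior exposure and to risk during follow-up, and timing relative to exposure is part of the trial's own argument. Such a variable is a natural covariate. Without it, nothing in the design or the model deals with a chance difference in year mix between arms, and any outcome variation that year explains stays in the error.

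The early-graduation comparison is a separate matter, because it is not randomised. Someone far from qualifying in spring 2020 presumably could not have endorsed the item, and nor could someone who had already qualified. Endorsers and non-endorsers would then differ in career stage as well as in pandemic deployment, and a difference in PTSD or MDD rates could not be assigned to either.

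**Working it through.** **1. The plan's own figure.** Protocol 11.2 gives a two-year risk of 25% (including subsyndromal cases), a 50% relative reduction, 80% power and α = 0.05. The SAP makes tests two-sided.

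- OR = (0.125/0.875)/(0.25/0.75) = 0.429, as stated.
- n per arm = [1.960·√(2 × 0.1875 × 0.8125) + 0.842·√(0.1875 + 0.1094)]² / 0.125² = 152.
- Two arms: 304. Three arms: 456. With 20% attrition: 456/0.8 = 570, or 190 per arm.

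The sample size reproduces exactly, and adding a covariate leaves it unchanged.

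**2. Precision given up.** The documents give no year mix and no risk by year. Assume equal thirds and control risks of 25% − g, 25% and 25% + g. The share of outcome variance explained by year is 1 − (mean within-year variance)/(0.25 × 0.75).

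| g (points) | Within-year variance | Share explained | × 152 per arm |
|---|---|---|---|
| 5 | 0.1858 | 0.9% | about 1 |
| 10 | 0.1808 | 3.6% | about 5 |
| 15 | 0.1725 | 8.0% | about 12 |

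The primary model is logistic, so this is an approximate guide to the gain rather than an exact saving.

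**3. Chance imbalance.** For a year group with share 1/3, the SD of the between-arm difference in share is √(2 × ⅓ × ⅔ / n).

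- n = 190 (randomised): SD 4.8 points, 95% range ±9.5.
- n = 152 (after attrition): SD 5.4 points, 95% range ±10.6.

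If that group's risk differs from the rest by 5 to 15 points, the risk difference between arms shifts by range × gap:

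- n = 190: 0.095 × 5 = 0.5 to 0.095 × 15 = 1.4 points.
- n = 152: 0.106 × 5 = 0.5 to 0.106 × 15 = 1.6 points.

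The planned difference is 25 − 12.5 = 12.5 points. Under the steeper assumption in step 2, where risk climbs by g with each successive year, the range at n = 152 is 1.96·√(2 × ⅔ / 152) × g = 0.184g, or 0.9 to 2.8 points.

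**4. Could the trial estimate a different effect by year?** Take RR 0.50 in an early-year group and 1.0 in the rest, 152 per arm, and a Wald test on the difference in log odds ratios. Each cell contributes 1/[n·p(1 − p)] to the variance.

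- Early group one third (about 51 and 101 per arm): SE = √(0.105 + 0.180 + 0.053 + 0.053) = 0.625; 0.847/0.625 = 1.36; power 27%.
- Early group one half (76 and 76 per arm): SE = √(0.070 + 0.120 + 0.070 + 0.070) = 0.575; 0.847/0.575 = 1.47; power 31%.
- With RR 0.75 instead of 1.0 in the rest, power is 11% and 13%.

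**5. Early-graduation comparison.** No arithmetic applies. Three years are eligible, the trial started in October 2017, and non-endorsers are not limited by stage. The non-endorser group can therefore include students too junior to graduate early and people who had already qualified.

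**The case against.** The case against making much of this is good. Randomisation keeps the arm comparison unbiased whether or not year is modelled, covariate choice is partly a matter of judgement, and the sizes in steps 2 and 3 are small. The Covid comparison is exploratory and is not between arms, so it cannot alter the trial's main inference. All of that stands.

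Three stronger readings are tempting, and the documents support none of them.

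- **A reader might infer that the trial loses the question of training before exposure.** It does not. Exposure is measured directly: the trauma screener is scheduled at all five time points (Protocol Appendix B), and baseline trauma exposure is a named moderator in the protocol objectives, the Process Evaluation section and the SAP's tertiary objectives. The SAP's tertiary model writes predictor main effects and predictor-by-time terms but no predictor-by-arm term. That weakens the analysis, but it is a separate issue from year of training.
- **A reader might infer that graduation turns standard practice into a second comparator.** Neither course length nor support after graduation is documented, and the top-priority contrast is iCT-R versus Mind-Online, with matched support in both arms.
- **A reader might infer heavy dilution of the effect.** If RR 0.50 held only in an early-year third, the pooled RR would be ⅓ × 0.5 + ⅔ × 1.0 = 0.83. That assumes no benefit at all in the other years, which nothing in the documents suggests. With RR 0.75 there, it is 0.67.

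What remains is that year costs almost nothing to include, and that the early-graduation comparison as written cannot be interpreted.

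**Conclusion.** The point holds as a modest one. Leaving year of training out causes no bias. It forgoes precision worth about 1 to 12 participants per arm. It also leaves unadjusted a chance imbalance that would typically move the risk difference by up to about 0.5 to 1.6 points (at most about 2.8 under the steepest gradient considered), against 12.5 planned. These sizes rest on assumed equal thirds and risk gaps of 5 to 15 points, since the documents supply neither.

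The early-graduation comparison is confounded by career stage, on the presumption that only students near qualification in spring 2020 could endorse the item. This affects an exploratory result only. That later-year students start with more exposure is plausible but not shown by any figure in the documents.

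**What to change.** 1. **SAP 6.2, primary and secondary models:** add year of training at randomisation (1, 2 or 3) as a fixed covariate. The cost is two more parameters, using information already collected for eligibility. Randomisation is complete, so the stratification stays as it is.
2. **SAP 6.6, early-graduation item:** restrict the comparison to participants in their final year in spring 2020. The cost is a smaller comparison group. Final-year status also has to be derived from year and date of entry and course length, and the documents do not state course length.
3. **Optional:** report the iCT-R effect by year of training with confidence intervals, labelled exploratory, and state that power for an arm-by-year interaction is only about 27 to 31% even for RR 0.50 versus 1.0.

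This point calls for no change to the sample size or to the description of standard practice.

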#### 7.1.2. Exclusion Criteria

- Current symptoms of PTSD or MD requiring treatment

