### 11.2 The Number of Participants

We plan to recruit 570 participants.

The risk of student paramedics developing full syndromal PTSD and MD over two years without intervention is 10% (1), and 25% if subsyndromal PTSD and MD that cause significant distress are included. We predict that our intervention will reduce the relative risk by 50%. Setting power at 80%,  $\alpha=.05$  and hypothesizing a reduction of relative risk of 50% gives an odds ratio of 0.429, which requires a total sample size of N=304 to show a risk reduction of 50% between the active and placebo intervention. Thus, each condition would require N=152. Since we have a third condition (no-training control), the total sample size required would be N=456. Allowing for a 20% rate of attrition, we will require a total sample size of N=570.

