## 15. Trial Flow Chart

[figure not shown]

659 APPENDIX B: SCHEDULE OF PROCEDURES  
660

| Procedures                                             | Assessments |         |          |          |           |
|--------------------------------------------------------|-------------|---------|----------|----------|-----------|
|                                                        | Baseline    | 6-weeks | 24-weeks | 52-weeks | 104-weeks |
| Informed consent                                | X           |         |          |          |           |
| Screening                                       |             |         |          |          |           |
| PHQ-9                                                  | X           | X       | X        | X        | X         |
| PCL-5                                                  | X           | X       | X        | X        | X         |
| Randomisation                                   | X           |         |          |          |           |
| Interviews                                      |             |         |          |          |           |
| Structured Clinical Interview DSM-5: PTSD & MD modules | X           | X       |          | X        | X         |
| Questionnaires                                  |             |         |          |          |           |
| CD-RISC                                                | X           | X       |          | X        | X         |
| Wagnild                                                | X           | X       |          | X        | X         |
| GAD-7                                                  | X           | X       |          | X        | X         |
| Smoking & Alcohol                                      | X           | X       |          | X        | X         |
| Weight                                                 | X           | X       |          | X        | X         |
| ISI                                                    | X           | X       |          | X        | X         |
| GHQ                                                    | X           | X       |          | X        | X         |
| WEMWBS                                                 | X           | X       |          | X        | X         |
| EQ5D5L                                                 | X           | X       |          | X        | X         |

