## **Randomisation and Blinding**

Participants are randomised on a 1:1:1 ratio as per a computer-generated randomisation schedule by OCTRU (Oxford Clinical Trials Research Unit) stratified by site, gender and baseline PHQ-9 score ( $\geq 9$  vs.  $< 9$ ) and PCL-5 score ( $\geq 33$  vs.  $< 33$ ). The researchers inform participants of the intervention they are to receive after participants have completed baseline assessments. Outcome assessment is single blind. Online questionnaires throughout the intervention and follow-up time points are completed without any involvement of the researchers. The clinical interview is done by an independent assessor, who is blind to treatment allocation. All personnel involved in the blood and saliva samples are blinded to intervention allocation. Due to the nature of the interventions, participants cannot be completely blinded to allocation.

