## **TRIAL POPULATION AND DESCRIPTIVE ANALYSES**

### **Representativeness of Study Sample and Patient Throughout**

Paramedic students aged 18 and above in the years 1, 2 or 3 of their paramedic training programme are eligible for the study. They are screened for levels of PTSD and MD, and a trained research assistant under supervision of the Principal Investigator will contact participants if they score in the clinical range on measures of PTSD or MD, or report suicidal ideation to evaluate whether they are eligible or need treatment. Participants will be excluded from the study if their symptoms are interfering with their lives and they would like treatment, and the research assistant will then offer information on evidence-based treatment in their local area.

The flow chart of participants through each stage of the trial, including numbers of participants randomly assigned, receiving the intervention, completing the study protocol, and analysed for the primary outcome is provided following current CONSORT guidelines.

Protocol violations or deviations and information relating to the screening data including potential numbers of ineligible patients randomised, together with reasons, are also described.

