Measures to test the tertiary trial objective are risk factors and predictors at baseline, such as level of social support (adapted from a brief measure of social support), trauma exposure (trauma screener), demographic data (general information questionnaire), neuroticism as a personality factor (subscale neuroticism from the Eysenck Personality Questionnaire), level of concrete thinking (CAT), and frequency, duration, and distress with regards to intrusive memories (Intrusions Questionnaire).

More information on the outcome measures can be found in the published trial protocol ([name] et al., 2018).

Time points:

Data are collected at pre-intervention, post-intervention, at 6-months follow-up, at 1-year follow-up and at 2-years follow-up. PTSD and MDD diagnoses are assessed pre-intervention, post-intervention, at 1-year and at 2-years follow-up, PTSD and MDD symptom severity are assessed at all measurement points. Secondary outcome measures are assessed at pre-intervention, post-intervention, and at 1-year and at 2-years follow-up. All measures for the tertiary trial objective are assessed at pre-intervention, at 1-year and at 2-years follow-up. All tertiary measures (except for demographics) are assessed at post-intervention, and trauma exposure, concrete thinking and intrusion measures are collected at 6-months follow-up, as well.

For the early analysis of the trial results, 1-year follow-up is the short-term primary outcome time point. Once the trial has been completed, the primary outcome time point is 2-years follow-up as described in the published trial protocol.

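### The primary diagnosis models name no baseline SCID term, and no planned analysis separates new onset from persistence of a disorder that may already be present at entry

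*Combined protocol and SAP*

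**What the plan says.** **Who can be randomised.** Protocol 7.1.2 has one exclusion: "Current symptoms of PTSD or MD requiring treatment". The SAP (Representativeness of Study Sample) applies it more narrowly: "Participants will be excluded from the study if their symptoms are interfering with their lives and they would like treatment". Protocol 8.2 reads much like the SAP. None of these places makes a baseline SCID diagnosis an exclusion. People above the screening cut-offs are expected in the trial: Protocol 8.4 has allocation "stratified by site and initial eligibility (above or below cut-off on PHQ-9 and PCL-5 at screening", and the SAP (Randomisation and Blinding) has it "stratified by site, gender and baseline PHQ-9 score" (9 or more) and PCL-5 score (33 or more).

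**What is measured at baseline.** Protocol Appendix B marks "Structured Clinical Interview DSM-5: PTSD & MD modules" at baseline, 6, 52 and 104 weeks. The SAP (Outcome Definitions) agrees: "PTSD and MDD diagnoses are assessed pre-intervention, post-intervention, at 1-year and at 2-years follow-up".

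**What is analysed.** The primary outcome is SCID-5 PTSD and MDD diagnoses at 1 and 2 years, in logistic mixed models on all randomised participants. On adjustment, the SAP says that "baseline PTSD symptom severity and MDD symptom severity and randomisation factors are added as covariates in these models", with site as a random factor. Secondary outcomes are each adjusted for their own baseline value as well.

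**What the sample size assumes.** Protocol 11.2 starts from "The risk of student paramedics developing full syndromal PTSD and MD over two years" without intervention. It puts this at 10%, or 25% with distressing subsyndromal cases included, and assumes that the intervention halves it.

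**The concern.** The trial is titled and sized as a prevention trial. Its primary outcome is whether a participant has a diagnosis at follow-up, whatever the status at entry. A participant who is a case at baseline and still a case at 1 year therefore counts the same as one who fell ill after randomisation. A participant who is a case at baseline and recovers counts as a non-case.

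Two things follow if baseline cases are present. First, a difference between arms could reflect fewer new cases, more remission, or both, and no planned analysis would tell these apart. Second, baseline diagnosis is likely to be a strong predictor of later diagnosis. It is collected, yet the models use symptom scores and cut-offs in its place.

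At stake are the interpretation of the main result and, under some assumptions, part of the power. The validity of the randomised comparison is not at stake.

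**Working it through.** **Step 1. Reproduce the plan's figure.** Inputs from Protocol 11.2 and 11.3 and the SAP: control risk 0.25, risk ratio 0.50 (so 0.125), two-sided alpha 0.05, power 80%.

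- Odds ratio = (0.125/0.875)/(0.25/0.75) = 0.429, as stated.
- The two-proportion formula with pooled variance and no continuity correction gives 152 per arm, hence 304 for two arms, 456 for three, and 456/0.8 = 570.
- Power = Φ[(|p1 − p2| − 1.96·SE0)/SE1], where SE0 uses the pooled proportion and SE1 the separate ones. At 152 per arm: SE0 = √(0.1875 × 0.8125 × 2/152) = 0.0448 and SE1 = √((0.1875 + 0.1094)/152) = 0.0442. Power = Φ[(0.125 − 0.0878)/0.0442] = 80.0%.

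The 25% includes subsyndromal cases. It is used below because it is the rate that reproduces 570.

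**Step 2. Let part of the 25% be persistence.** The documents give neither the share of baseline cases nor how many persist, so these are assumptions:

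- b = share of randomised participants with a baseline diagnosis, 3% to 10%.
- Half of them are still cases at follow-up in the control arm, so q = b/2 of the 25% is persistence.
- New onset is halved by iCT-R, as planned.
- r = proportion by which iCT-R reduces persistence.

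Risk in iCT-R = (0.25 − q)/2 + q(1 − r).

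| b | q | r | iCT-R risk | Risk ratio | Power, 152 per arm |
|---|---|---|---|---|---|
| 3% | 0.015 | 0 | 0.1325 | 0.53 | 74% |
| 10% | 0.05 | 0 | 0.15 | 0.60 | 59% |
| 3% | 0.015 | 0.25 | 0.1288 | 0.515 | 77% |
| 10% | 0.05 | 0.25 | 0.1375 | 0.55 | 70% |
| 3% or 10% | 0.015 or 0.05 | 0.50 | 0.125 | 0.50 | 80% |

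Example, row 2: SE0 = √(0.20 × 0.80 × 2/152) = 0.0459 and SE1 = √((0.1875 + 0.1275)/152) = 0.0455. Power = Φ[(0.10 − 0.0899)/0.0455] = 59%.

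**Step 3. The new-onset set under the same assumptions.** n per arm = 152(1 − b); control risk = (0.25 − q)/(1 − b), halved in iCT-R.

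- b = 3%: about 147 per arm, 24.2% vs 12.1%, power 77%.
- b = 10%: about 137 per arm, 22.2% vs 11.1%, power 70%.

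These figures are for a combined outcome at the planning rate. Analyses of one disorder at a time have fewer events and less power.

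**Step 4. A different set-up as a check.** Suppose that 25% vs 12.5% applies to those without a baseline diagnosis, and that baseline cases (5-10%, with 30-70% persisting equally in both arms) come on top. Power for the all-randomised outcome is then about 75-63%, and about 78-76% in the new-onset set. The direction does not depend on the set-up, but the size does.

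**The case against.** **The outcome fits the stated objective.** The primary question in Protocol section 5 is about fewer cases and fewer symptoms at follow-up, and the SAP (Objectives) speaks of diagnoses at 1 and 2 years. Follow-up status answers that. The idea of developing disorder enters through the title and the sample-size text. This stands, and it is why the primary analysis should stay as it is.

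**The models already carry much of the information.** They include continuous PCL-5 and PHQ-9 severity, both cut-offs, site and gender, so it would be wrong to say that they adjust for symptom scores alone. The general mention of baseline scores as fixed effects is not spelled out for the binary outcome. Where the SAP does spell it out for diagnosis outcomes, in the tertiary models, it means symptom severity. So part of the prognostic value is recovered, but diagnosis itself is not named.

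**Baseline status is not ignored.** Past and current comorbidities are tertiary moderators, and a subgroup display splits the primary outcome by baseline severity. Neither is a new-onset analysis, and the listed sensitivity analyses concern missing data.

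**Baseline cases may be few or none.** A reader might infer that people meeting SCID criteria were enrolled. The documents show only that they could be. People who screen in the clinical range are contacted, and some are then excluded. No baseline SCID count is given.

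**The power loss needs a one-sided assumption.** It is largest when training does nothing for existing cases. The protocol's Background says that the team's preventive work drew on a core technique of its PTSD treatment, so some benefit is plausible. If persistence is also halved, nothing is lost. The calculation is also unadjusted, whereas the planned model is not.

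**Timing of the baseline SCID.** Appendix B lists SCID and randomisation under the same baseline column. The SAP says that participants learn their allocation after the baseline assessments. This supports use as a covariate, but the order relative to randomisation should be confirmed.

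**Conclusion.** The point holds as a gap in what the primary result can show. Eligibility leaves room for baseline cases, the diagnosis models name no baseline SCID term, and nothing planned separates new onset from remission or persistence.

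Three stronger readings are not supported. A reader might infer that the comparison is biased. It is not: randomisation, stratification and analysis of all randomised participants protect it. A reader might infer that the primary outcome is the wrong one, but it matches the written objective. A reader might infer that power has fallen to 59%. That is one end of an illustration, and the other end is no loss at all.

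The size is unknown because the documents give neither the number of baseline cases nor their persistence. On the assumptions above, power runs from 59% to 80% for the planned outcome and from 70% to 77% for the new-onset set. The case for change rests mainly on interpretability and low cost, not on a demonstrated loss of power.

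**What to change.** 1. Keep the ITT analysis of diagnosis at follow-up as primary.
2. Add baseline SCID PTSD and MDD status as covariates in the diagnosis models. State a fallback if baseline cases are too few for stable estimation, such as penalised estimation or dropping the term.
3. Pre-specify a supportive analysis, for each disorder, of SCID diagnosis at 1 and 2 years among participants SCID-negative for that disorder at baseline. The set is defined by baseline status, so the arms remain comparable as randomised. Confirm that the baseline SCID preceded allocation or was completed blind to it.
4. Report the number of baseline cases by arm, and persistence among them by arm.
5. Reconcile the exclusion wording in Protocol 7.1.2 with that in Protocol 8.2 and the SAP (Representativeness of Study Sample). No eligibility rule is proposed here.

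The cost is SAP wording, best settled before outcomes are compared by arm. The baseline SCID is already in the schedule. The downside is a somewhat smaller set for the supportive analysis (about 147 to 137 per arm instead of 152 if 3-10% are baseline cases), so it should be read for its estimate and interval alongside the primary result.
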